### Statistical analysis

An intention-to-treat analysis will be performed and missing data will be input with the last-observation-carried-forward method. Continuous variables will be presented as the mean and the SD or the median and the interquartile range (IQR) according to the normality assumption using the Kolmogorov-Smirnov test. Categorical variables will be presented as numbers of patients and proportions.

The primary outcome (the initial PAED score) will be compared with an independent *t* test or a Mann-Whitney *U* test. For secondary outcomes, continuous variables will be compared with an independent *t* test or the Mann-Whitney *U* test and categorical variables will be compared with Pearson’s chi-squared test or Fisher’s exact test. All tests are two-sided and *P* < 0.05 is considered statistically significant. A statistician ([name]) who is not involved in the data collection will conduct all statistical analyses with SPSS software (version 21.0; SPSS Inc., IBM, Chicago, IL, USA).

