## Background

Emergence delirium (ED) is described as a “mental disturbance during recovery from general anesthesia consisting of hallucinations, delusions and confusion manifested by moaning, restlessness, involuntary physical activity, and thrashing about in bed” [1]. It can cause self-injury, dressing disruptions, surgical dehiscence, and dislodged indwelling catheters and can lead to parents’ and surgeons’ dissatisfaction with the anesthetic. The incidence of ED in pediatric patients after general anesthesia is reported to be between 10 and 80% [2]. Several factors, such as sevoflurane or desflurane anesthesia, younger age, pain, anxiety and the temperament of the child have been suggested to contribute to ED, but the precise etiology remains uncertain [2, 3]. Various studies have tried to reduce emergence delirium after anesthesia [4–6], but none have been completely effective.

Mothers usually spend a large amount of time with their children. Therefore, mothers can be assumed to contribute to their children’s emotional status and neurological development. In a previous study, maternal voice had special importance and enhanced involuntary attention [7]. Moreover, a mother’s voice elicited stronger activations in specific cerebral regions than an unknown voice in another study [8]. A recorded mother’s voice increased the activation of the prefrontal cortex compared to a stranger’s voice [9]. As shown by these studies, a mother’s voice has been shown to have a strong impact on both behavioral and neuronal responses in children.

However, the influence of a familiar voice, especially a mother’s voice, on a child during anesthetic emergence has been scarcely explored previously. Therefore, we will investigate whether maternal voice supports emotional stability and facilitates emergence during the emergence period. We hypothesized that children would show reduced ED and faster emergence when they heard their mothers’ recorded voices compared to a stranger’s recorded voice.

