### Measurements

The primary outcome measurement is the initial PAED score in the PACU. The secondary outcomes are hemodynamic parameters (heart rate, mean blood pressure), the duration of time from the cessation of anesthetics to a BIS score of 60/70 and 80 (BIS > –60/70/80 time), the eye-opening or purposeful movement time, the extubation time, the total consumption of analgesics, PACU stay time, and PAED, Watcha, and FLACC scores in the PACU.

The Modified Yale Preoperative Anxiety Scale (m-YPAS) will be used when the patients arrive at the preoperative waiting room with their parents before premedication [10, 11]. At the end of surgery, all anesthetics will be stopped immediately and the BIS value and the end-tidal sevoflurane concentration (ET_sevo_ %) are recorded. Hemodynamic parameters, including heart rate (HR) and mean blood pressure (MBP), will be checked at five time points; at the time of the cessation of anesthetics (baseline, t_0_), time to reach a BIS value of 60 (t_1_), time of extubation (t_2_), time of PACU arrival (t_3_), and time of PACU discharge (t_4_). BIS > 60, 70, and 80 times, defined as the time intervals from the cessation of anesthetics until the BIS reached values of 60, 70, and 80, respectively, will be measured. Eye-opening or purposeful movement time is defined as the interval from the cessation of anesthetics to-eye opening or purposeful movement of the patient. Extubation time, defined as the interval from the cessation of anesthetics until extubation, will also be measured.

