### Sample size

The primary outcome is the initial PAED score. In our pilot study, the mean difference of the PAED score between the stranger group and the maternal group was 1.6 with a standard deviation (SD) of 2.19. To attain an alpha value of 0.05 and a test power of 0.8, 30 patients are needed in each group using the following formula [16]. We plan to enroll a total of 66 patients to allow for a 10% dropout rate:$$ n\kern0.5em =\kern0.5em \frac{2{\left({z}_{a/2}+{z}_{\beta}\right)}^2\kern0.5em \cdotp \kern0.5em {\sigma}^2}{{\left({\mu}_c-{\mu}_t\right)}^2} $$

To compensate for the possibility of an over-estimated effect size of the pilot study, we will perform an interim analysis at 50% enrollment. If the sample size has significantly lower power than our expectation, we will recruit more patients. Otherwise, we will continue the study according to our initial sample size calculation.

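### The primary comparison names two unadjusted tests without saying which applies, and makes no use of baseline anxiety or age

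*Protocol article*

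**What the plan says.** The Measurements section fixes the endpoint: "The primary outcome measurement is the initial PAED score in the PACU". The Statistical analysis section then offers two ways to compare it: "The primary outcome (the initial PAED score) will be compared with an independent *t* test or a Mann-Whitney *U* test". Both are two-group tests without covariates, and no sentence says when each applies. A Kolmogorov-Smirnov check appears one paragraph earlier, where the choice between mean with SD and median with IQR for describing continuous variables is made "according to the normality assumption using the Kolmogorov-Smirnov test". On the error rate: "All tests are two-sided and *P* < 0.05 is considered statistically significant".

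The Sample size section works with means. In the pilot, "the mean difference of the PAED score between the stranger group and the maternal group was 1.6 with a standard deviation (SD) of 2.19", and from this, "To attain an alpha value of 0.05 and a test power of 0.8, 30 patients are needed in each group".

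On baseline information, the Measurements section says: "The Modified Yale Preoperative Anxiety Scale (m-YPAS) will be used when the patients arrive at the preoperative waiting room", before premedication. Age (2 to 8 years) and surgical specialty (ophthalmology or otorhinolaryngology) are known from eligibility. The Background reports that "younger age, pain, anxiety and the temperament of the child have been suggested to contribute to ED", while adding that the etiology is uncertain. Randomisation is 1:1, and no stratification is described.

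**The concern.** Two things are at stake.

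First, the primary analysis is not one analysis. The t test addresses a difference in means, the quantity on which the trial is sized. Mann-Whitney addresses whether scores in one arm tend to exceed those in the other, and gives no estimate of the 1.6-point difference. With both named and no rule, the choice can be made after the data are seen, and the two P values need not fall on the same side of 0.05.

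Second, the trial measures a baseline score that it regards as potentially prognostic and gives it no role in the stated primary comparison. In a trial of 66 children, sized on a pilot effect that the Sample size section concedes may be too large, any precision already paid for is worth using.

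**Working it through.** **Inputs from the protocol article.** Difference 1.6, SD 2.19, two-sided alpha 0.05, power 0.80, 30 per group (Sample size, Statistical analysis). **Assumed:** the multiple correlation r between the covariates and initial PAED, and the shape of the PAED distribution. The documents give neither.

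**Step 1: the plan's own figure.** n = 2 × (1.960 + 0.842)² × 2.19² / 1.6² = 29.41, rounded up to 30 per group. This reproduces the stated number. It is a formula for an unadjusted difference in means. The exact t test at 30 per group has noncentrality (1.6/2.19) × √(30/2) = 0.7306 × 3.873 = 2.830 on 58 degrees of freedom, so power is 0.795.

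**Step 2: covariate adjustment.** The residual SD becomes 2.19 × √(1 − r²), so the noncentrality becomes 2.830 / √(1 − r²). Three covariates (m-YPAS, age, surgery type) reduce the degrees of freedom from 58 to 55.

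| Assumed r | Residual SD | Noncentrality | Power at 30 per arm |
|---|---|---|---|
| unadjusted | 2.19 | 2.830 | 0.795 |
| 0 | 2.19 | 2.830 | 0.79 |
| 0.2 | 2.15 | 2.888 | 0.81 |
| 0.3 | 2.09 | 2.966 | 0.83 |
| 0.5 | 1.90 | 3.267 | 0.89 |

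These figures treat the covariates as balanced between arms. With simple randomisation, three unrelated covariates explain on average 3/59 = 0.051 of the variation in arm by chance, which multiplies the noncentrality by about √(1 − 0.051) = 0.974. Power then falls by one to two points, to about 0.77, 0.79, 0.81 and 0.88. On that stricter reckoning, adjustment breaks even at about r² = 0.051, that is r = 0.23.

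**Step 3: what the open choice of test does.** Rounded PAED-like scores were simulated with SD 2.19, 30 per arm and 4,000 runs per setting, for one roughly normal and two skewed shapes (all assumed).

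- Type I error, t test alone: 4.8–5.2%.
- Type I error, Mann-Whitney alone: 4.9–5.2%.
- Type I error, test selected by a Lilliefors-corrected Kolmogorov-Smirnov rule: 4.9–5.3%.
- Type I error, smaller of the two P values reported: 6.0–6.3%.
- Power at a 1.6-point difference, roughly normal scores: t 78.6%, Mann-Whitney 77.2%.
- Power at a 1.6-point difference, skewed scores: t 79–80%, Mann-Whitney 86–98%.

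The Monte Carlo standard error at 5% is √(0.05 × 0.95 / 4000) = 0.34%, so the first three lines cannot be told apart from 5%. The power figures show that the two tests can disagree when scores are skewed.

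**The case against.** The strongest reply is that nothing here is invalid. Under 1:1 randomisation an unadjusted test is sound, it matches the sample-size formula, and that formula reproduces. This stands. A reader might infer that a chance imbalance in anxiety or age would bias the primary contrast. It would not: such imbalance is ordinary sampling error, already reflected in the standard error.

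The precision gain is also assumed. The m-YPAS is taken before ketamine premedication, so a strong link to a PACU score cannot be presumed, and at weak correlations the gain is nil or slightly negative. This stands as a limit on size.

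Three further inferences are tempting and unsupported.

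- That Kolmogorov-Smirnov selects the primary test. The text ties it only to how data are presented. Selection is a natural reading, but an inference.
- That an integer score would usually fail the check and push the analysis to Mann-Whitney. For rounded-normal scores, a Lilliefors-corrected test rejected in about two thirds of simulated trials and plain Kolmogorov-Smirnov in about 2%. The article does not say which version is meant, so no switching rate can be claimed.
- That the article calls anxiety and age established determinants of delirium. It says only that they have been suggested to contribute.

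It can also be said that Mann-Whitney may be the more powerful test for skewed scores. That is true in the simulations, and is a reason to keep it as a named sensitivity analysis. It still does not estimate the quantity on which the trial is sized.

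Finally, an analysis plan that is not shown may settle the test and covariates. But the article does not leave the primary test for later: it states two alternatives. That part of the point does not depend on the missing document.

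**Conclusion.** The point holds as one of an unfixed primary test and unused precision. Bias, an invalid analysis and a wrong sample size are not shown.

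The part about the test rests on the text alone: two tests of different quantities, no stated rule, and a sample size built on one of them. Type I error stays near 5% with either test, or with the Lilliefors-based selection rule simulated here. About 6% is what happens if the smaller P value is chosen, which the plan does not say will be done.

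The part about covariates rests on an assumed correlation. Across r from 0 to 0.5, adjusted power at 30 per arm runs from about 0.79 to 0.89 against 0.795, or from about 0.77 to 0.88 once chance imbalance is allowed for. The likely loss is therefore small and the possible gain moderate. The change is worth making, but its size cannot be settled from the documents.

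**What to change.** Before unblinding, and before the interim analysis at 50% enrolment if that is still ahead, name one primary analysis: a linear regression (ANCOVA) of initial PAED on arm, m-YPAS, age and surgery type, reporting the adjusted mean difference with a 95% CI from robust or bootstrap standard errors. Keep Mann-Whitney as a named sensitivity analysis, reported whatever its result. State that the Kolmogorov-Smirnov check governs descriptive presentation only and does not select the primary test.

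The cost is wording and about 3 degrees of freedom. The m-YPAS is already scheduled, and age and specialty are known at eligibility. Sample size, visits and procedures are unchanged.

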## Discussion

The effect of a mother’s voice elicited positive physiologic and behavioral responses in other clinical territories [17–19], but this has been scarcely reported in perioperative settings. In a study by Kim and colleagues [20], a mother’s recorded voice reduced preoperative anxiety and emergence agitation during cardiac catheterization using ketamine sedation. However, the quality of mothers’ voices was not standardized and the control group did not receive any voice stimuli. In contrast, we had the mothers read the same dialogue in a calm environment in all study populations and compared the mothers’ voices with the stranger’s voice. Additionally, we measured the BIS to quantify the sedation level and the effects of a mother’s voice on the emergence of her child compared with a stranger’s voice. Other major differences are the level of anesthesia and the surgical stimuli. Our study involves investigation under general anesthesia using both ketamine and sevoflurane inhalation, but Kim’s study was conducted under modest sedation using ketamine only [20]. Sevoflurane or desflurane anesthesia is believed to contribute to a higher frequency of emergence delirium [21].

In this study, patients are premedicated with ketamine before entry to the operating room. Various agents have been shown to be beneficial effect on prevention of ED [3–6, 22–24]. Among the numerous drugs, a new selective α_2_-agonist, dexmedetomidine has recently been spotlighted as an effective prophylactic and treatment agent for ED [2, 6, 22]. Despite the ongoing encouragement from the previous findings, however, there have been no officially approved indications for its use in the pediatric population. Meanwhile, ketamine has been safely used in pediatric anesthesia for over five decades. It effectively decreased the incidence of emergence delirium in previous studies [23, 24]. Moreover, it was equally effective as dexmedetomidine in a study after strabismus surgery with sevoflurane [25]. Taken all together, we thought that ketamine would be suitable for our settings.

To our knowledge, this is the first randomized controlled trial to investigate the advantage of a mother’s recorded voice during the emergence period on the pediatric emergence profile after general anesthesia. If the study is successful, this research will establish a new prophylactic option to decrease emergence delirium and enhance the wake up after general anesthesia.

### Trial status

Patient recruitment is still ongoing since November 2016.

## Abbreviations

BIS: Bispectral Index
FLACC: Face, Legs, Activity, Cry and Consolability
m-YPAS: Modified Yale Preoperative Anxiety Scale
PACU: Post-anesthesia care unit
PAED: Pediatric Assessment of Emergence Delirium
